**Fig. 2 Fig2:**
[figure not shown]
Translated interface of *MyKid’sNutrition* app: **a** login page; **b** sign-up page, which appears in the first use; **c** home page; **d** user’s profile page; **e** add measurements page; **f** topics page, each topic contains several contents; and **g** growth charts page, which demonstrates weight for age, height for age, BMI for age, and weight for height charts

The *MyKid’sNutrition* app was designed and developed by a team of nutritionists, pediatricians, designers, and developers. In the process that lasted for about one year, nutritionists and pediatricians initially provided the desired and required features to the design and programming team. A prototype of the application was designed, then existing problems were reported to the development team. After several upgrades, the final version of the application was eventually prepared. In order to prepare the content of the app, a team of nutritionists and pediatricians discussed nutrition educational content in numerous meetings derived entirely from scientific references. After the necessary corrections, the final version of the educational content was used in the application. User-manual of *MyKid’sNutrition* app is provided as Supplementary material 1.

### Content validity

To assess the quantification of content validity, we selected a Content Evaluation Panel consisting of ten content experts and ten lay experts. While the lay experts were potential research subjects, content experts were professionals with research experience or work in the field. Panel members were asked to judge the content validity ratio (CVR) and the content validity index (CVI). We listed the *MyKid’sNutrition* app’s content and provided it to the panel of experts as an evaluation list along with the printed content. The CVR was determined by asking each panelist, independently from the others, to indicate whether each item was “essential,” “useful,” or “not necessary.” The responses of all panelists were pooled to determine the percentage of items considered as “essential.” CVR was defined as (nE—n/2)/(n/2), where Ne was the number of panelists who indicated “essential” and N was the total number of panelists. Lawshe’s table was used to determine whether the CVR was approved [22]. The number of panelists in our study was 20 people, and content validity of all items was approved (CVR > 0.42).

To check the CVI, three criteria of simplicity, relevance, and clarity were analyzed separately on a 4-part Likert scale for each item by a panel of experts. CVI was computed by dividing the number of experts giving a rating of 3 or 4 by the total number of experts. Items were accepted based on a CVI score above 0.80. Table 1 demonstrates the CVI scoring method [22, 23]. In our study, the average CVI for all contents was 0.95, 0.96, and 0.90 for simplicity, relevance, and clarity, respectively.

**Table 1 Tab1:** Scoring method for measuring content validity

Scores	**Simplicity**	**Relevance**	**Clarity**
1	Not simple	Not relevant	Not clear
2	Item need some revision	Item need some revision	Item need some revision
3	Simple but need minor revision	Relevant but need minor revision	Clear but need minor revision
4	Very simple	Very relevant	Very clear

#### Criteria for discontinuing or modifying allocated interventions {11b}

All subjects will be free to leave the study at any phase of the study for any reason without any consequences. Also, the research team will be free to remove any subject if they are uncooperative or lost to follow-up.

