#### Eligibility criteria {10}

The inclusion criteria will be as follows: children aged 2–6 years at baseline; mothers’ willingness to participate in the study and signing a written consent form; having a smartphone and willingness to use a smartphone application; mothers’ reading and writing skills; and confirmed malnutrition and underweight using growth charts.

There will be two exclusion criteria as follows: subjects suffering from a specific disease that can affect the results and those reluctant to continue participation in the study.

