#### Additional consent provisions for collection and use of participant data and biological specimens {26b}

The consent form will inquire whether participants consent to the use of their data in the event of withdrawal from the trial or share relevant data with people from the universities taking part in the research or from regulatory authorities, where relevant. This trial will not involve collecting biological specimens for storage.

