### Assignment of interventions: blinding

#### Who will be blinded {17a}

Due to the nature of the intervention, neither the research team nor the patients in both arms can be blinded to the patients’ allocation. However, the outcome assessment team, as well as those who are involved in data analysis and statistics will be blinded to the group allocations.

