#### Methods in analysis to handle protocol non-adherence and any statistical methods to handle missing data {20c}

Missing data will not be imputed. All available data will be used in the models.

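### An unblinded team may remove participants it finds uncooperative after randomisation, so the comparison may become a selected completers analysis with bias of unknown size and sign

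*Protocol article*

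**What the plan says.** The section on discontinuing or modifying interventions (11b) first lets participants leave at any time. It then adds that "the research team will be free to remove any subject if they are uncooperative or lost to follow-up". It does not define the term, set a time limit, or say whether a removed participant is still measured at 3 months.

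The blinding section (17a) says that "neither the research team nor the patients in both arms can be blinded", but that "the outcome assessment team, as well as those who are involved in data analysis and statistics will be blinded to the group allocations".

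The eligibility section (10) lists two exclusion criteria: "subjects suffering from a specific disease that can affect the results and those reluctant to continue participation in the study". The second of these arises only after a person has entered the study.

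The outcomes section (12) gives two measurement times, baseline and 3 months. The section on non-adherence and missing data (20c) reads in full: "Missing data will not be imputed. All available data will be used in the models". The statistical methods section (20a) names an unpaired t-test or a Mann–Whitney U test for quantitative outcomes, with covariate adjustment when needed.

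The consent section (26b) says that the form will ask "whether participants consent to the use of their data in the event of withdrawal from the trial".

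**The concern.** Randomisation makes the arms comparable only if what happens afterwards does not select who is compared. Here, staff who know the allocation have an open discretion to take people out of the study. Allocation follows directly on the baseline assessment, so most uncooperative behaviour, and all loss to follow-up, would show itself after allocation.

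The discretion need not work alike in the two arms. Both arms can miss contacts or visits, but only the intervention arm has an app to neglect. The adherence and retention sections (11c, 18b) have the team contact participants to raise compliance and remind them to use the app. How a mother engages is plausibly related to her knowledge, attitude and practice scores, which are trial outcomes.

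At stake is the question that the trial answers. The stated objective is the effectiveness of the app. A comparison of those whom staff chose to keep may instead describe the app's effect in cooperative users, set against a control group selected in another way.

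**Working it through.** **Inputs from the sample size section (14).** Alpha 0.05, power 0.80, effect size 0.5, 51 pairs per arm (102), 14% dropout, total 116.

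**The plan's own figures.** A two-sample t-test with d = 0.5, alpha 0.05 and power 0.80 needs 50.15 per arm one-sided, hence 51 per arm and 102 in total, as stated. The two-sided calculation needs 63.8, hence 64 per arm; that mismatch is a separate matter. The total follows from 102 × 1.14 = 116.28, stated as 116. If 14% of 116 are lost, 116 × 0.86 = 99.8 remain, about 50 per arm.

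**How removal reaches the estimate.** There is one post-baseline value per participant. If it is missing and not imputed, the participant contributes nothing to the t-test or Mann–Whitney comparison at 3 months.

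**Size, simple form.** Let a share p of one arm be lost, and let those lost have a mean g SD below those kept (mean K).
- Full-arm mean = (1 − p)K + p(K − g) = K − pg, so the kept mean exceeds the full-arm mean by p × g.
- p = 0.14 (the protocol's allowance, here taken as wholly selective, in the app arm only), g = 0.5 (assumed): 0.14 × 0.5 = 0.07 SD.
- g = 1.0 (assumed): 0.14 × 1.0 = 0.14 SD.
- Relative to the planned effect: 0.07 / 0.5 = 14% and 0.14 / 0.5 = 28%.

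**Type I error with no true effect.** Two-sided 5% t-test, 51 per arm, 100 degrees of freedom. The noncentrality is bias × √(51/2): 0.07 × 5.05 = 0.353 and 0.14 × 5.05 = 0.707. The noncentral t distribution gives rejection probabilities of 0.064 and 0.108.

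**Other patterns.** A simulation used 58 per arm, no true effect and 20,000 runs. Participants with the lowest cooperativeness were removed; cooperativeness correlates r with outcome. Removal rates by arm and r are assumptions.

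| Removed, app / control | r, app / control | Bias (SD, + favours app) | Type I error |
|---|---|---|---|
| 14% / 14% | 0.3 / 0.3 | about 0 | 0.06 |
| 14% / 14% | 0.3 / 0 | +0.07 | 0.065 |
| 14% / 14% | 0.5 / 0 | +0.13 | 0.10 |
| 24% / 4% | 0.3 / 0.3 | +0.10 | 0.08 |
| 24% / 4% | 0.5 / 0.5 | +0.16 | 0.14 |
| 4% / 24% | 0.3 / 0.3 | -0.10 | 0.08 |
| 14% / 14% | -0.3 / 0 | -0.08 | 0.07 |

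The rows with selection in the app arm only agree with the simple form. The last two rows show that the sign can reverse.

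**The case against.** The strongest reply is that the documents do not show where removals would fall. Being uncooperative is not tied to app use; it may mean a missed call or a missed visit in either arm. App reminders might even improve retention in the app arm and leave heavier losses among controls. A reader might infer that the rule biases the trial towards the app. The documents do not support that: the direction is plausible, but the table also holds zero and negative values.

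A reader might also infer that the plan is bound to become a completers analysis. That is too certain. Section 20c commits to using what data there are, and the consent form asks about data use after withdrawal. Together they leave room to keep a removed participant's data, but neither requires it, and neither requires the 3-month measurement to be sought.

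Third, the exclusion criterion on reluctance gives staff no power to remove anyone. It reads like voluntary withdrawal, and reluctance can show between consent and allocation without harm to randomisation. It is loose drafting that should be tidied, not a second removal rule.

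Fourth, declining to impute is not in itself an error. With one post-baseline value, imputing from the same baseline variables adds almost nothing to a baseline-adjusted available-data analysis. The lack of an explicit as-randomised statement would, taken alone, be a detail that a condensed article may leave to the full protocol or SAP.

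All four replies narrow the point. None removes the rule in section 11b. Blinding of assessors and analysts does not cure it, because selection happens before they see any data. Nor can an SAP recover 3-month values that were never collected.

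**Conclusion.** The point holds in limited form and should be fixed. The protocol states an undefined removal power, open after randomisation and held by staff who know the arm. With one outcome visit and available-data analysis, its use may turn the comparison into one of selected completers.

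The bias cannot be sized from the documents. The figures of +0.07 to +0.14 SD and 6.4% to 10.8% type I error rest on assumed selective loss of 14% in the app arm alone, with an assumed gap of 0.5 to 1.0 SD. They illustrate an adverse case and are not a prediction. Equal selection gives about zero, and other assumed patterns give -0.08 to -0.10 SD. What is established is the loss of protection against such bias, in either direction.

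**What to change.** 1. In section 11b, delete the team's right to remove uncooperative participants from the study.
2. In section 10, restrict reluctance to continue to the time before randomisation, or move it out of the exclusion criteria and treat it as voluntary withdrawal.
3. State that 3-month measurements are sought for everyone randomised, whatever their app use or cooperation, unless consent is withdrawn. State that all with a measurement are analysed in their allocated arm.
4. Keep the available-data main analysis in section 20c. Add one sensitivity analysis in which missing outcomes are imputed and shifted by a range of delta values, separately by arm.

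The cost is protocol wording, a few more visit attempts and one extra analysis. The consent form already has a question on data use after withdrawal. The downside is that non-users stay in the app arm and may dilute the estimated effect; for a question about effectiveness, that dilution belongs in the answer.

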#### Strategies to improve adherence to interventions {11c}

The research team will contact subjects regularly to solve any probable problems in a timely manner and increase the subjects’ compliance.

#### Relevant concomitant care permitted or prohibited during the trial {11d}

There will be no restrictions on the relevant concomitant care. In addition, all participants will be free to continue with their usual care.

#### Provisions for post-trial care {30}

No specific post-trial care is planned, as the study is a low-risk intervention. At the end of the study, all participants will be offered a report of their children’s nutritional status from the post-assessment, which will determine whether the children need any specific treatment.

#### Outcomes {12}

The outcomes of *MyKid’sNutrition* trial would be the change in the growth indicators and mothers’ nutritional knowledge, attitude and practice within the groups, and the differences between the groups. Weight for height and BMI for age *z*-scores, which are the growth indicators and mothers’ nutritional literacy, will be measured at baseline and after 3-month follow-up visits. Additionally, the participants’ demographic and socio-economic status will be measured.

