### Objectives {7}

In this RCT, the primary objective is to investigate the effectiveness of *MyKid’sNutrition* app on children’s nutritional status and maternal nutritional knowledge, attitude, and practices.

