#### Sample size {14}

To estimate the sample size, we performed a statistical power analysis based on previous studies [24] and considering an alpha equal to 0.05 and a power of 0.80 with an effect size of 0.5 using G*Power 3.1.9.7. Accordingly, the sample size was estimated as 102 participants (51 mother–child pairs in each group). Finally, considering a dropout rate of 14%, the total sample size was calculated as 116 people.

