### Data collection and management

#### Plans for assessment and collection of outcomes {18a}

We will use a questionnaire to collect all participants’ sociodemographic and baseline information, including name, sex, age, contact information, family size and income, past medical history, phone number(s), education, and occupation. The research team will measure all children’s anthropometric indices and the presence of undernutrition will be assessed based on growth charts [6]. Using a questionnaire with confirmed psychometric properties, the mothers’ nutritional knowledge, attitude, and practice will be assessed [25]. All data will be collected in a uniform and reproducible manner by trained data collectors. The quality of the data will be supervised by the principal investigator.

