### Statistical methods

#### Statistical methods for primary and secondary outcomes {20a}

We will use descriptive statistics for summarizing and determining the sample’s characteristics and distribution among the patients. Frequencies and proportions will be used to summarize categorical data. Analyzing associations between qualitative data variables will be done using the chi-square (*χ*^2^) test or Fisher’s exact test, as appropriate. The unpaired *t*-test or Mann–Whitney *U* test will be used to analyze quantitative data between the two independent groups. The analyses will be adjusted for age, sex, and other baseline characteristics as covariates when needed. A 95% confidence interval will be provided for all comparative analyses, and statistical significance for main effects will be determined as 5%.

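### No primary outcome is named under a compound primary objective, so the headline result can be chosen from five outcomes at 5% each

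*Protocol article*

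**What the plan says.** Protocol article, Objectives {7}, sets a single primary objective: the effect of the app on "children’s nutritional status and maternal nutritional knowledge, attitude, and practices".

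Outcomes {12} defines the outcomes as "the change in the growth indicators and mothers’ nutritional knowledge, attitude and practice within the groups, and the differences between the groups". It names two growth indicators, "Weight for height and BMI for age" z-scores, both measured at baseline and at 3 months. Plans for assessment and collection of outcomes {18a} adds that "the mothers’ nutritional knowledge, attitude, and practice will be assessed" by questionnaire. None of these is called primary or secondary.

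The heading of Statistical methods {20a} refers to primary and secondary outcomes, but neither that section nor any other says which is which. It states that an unpaired t-test or Mann–Whitney test "will be used to analyze quantitative data between the two independent groups", and that "statistical significance for main effects will be determined as 5" per cent. It gives no hierarchy, no adjustment and no rule that several outcomes must succeed together.

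Sample size {14} assumes an alpha of 0.05 and "a power of 0.80 with an effect size of 0.5", leading to 102 participants (51 per group) and 116 after dropout. It does not say which outcome the effect size belongs to.

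**The concern.** Naming the primary outcome decides what counts as success. Here it stays open: the objective is compound, the outcome list is flat, and the power calculation does not reveal which outcome was meant. Someone following the text could pick the headline outcome after seeing the results.

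The five outcomes are also not interchangeable. Mothers know their allocation (Who will be blinded {17a}), the app is educational, and the maternal domains are measured by questionnaire after three months of use. A gain on that questionnaire could be reported as meeting the primary objective of a trial in malnourished children with no change in growth. Outcomes {12} also lists change within each group, and such change says nothing about the app without a comparison with control.

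**Working it through.** **The plan's own figure.** Inputs from Sample size {14}: d = 0.5, alpha 0.05, power 0.80. For two independent means (noncentral t):

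- One-sided 5%: 50.15, rounded up to 51 per group, 102 in total, with power 80.6% at 51. This matches the plan.
- Two-sided 5%: 63.8, rounded up to 64 per group, 128 in total. This does not match.
- Dropout: 102 × 1.14 = 116.3, so 116.

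The stated size is therefore that of one comparison at one-sided 5%. Statistical methods {20a} does not state sidedness.

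**Number of outcomes.** Weight-for-height z and BMI-for-age z (Outcomes {12}), plus knowledge, attitude and practice (Outcomes {12}; Plans for assessment {18a}): 2 + 3 = 5. There is one follow-up time and no interim analysis.

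**Chance of at least one false significant difference, either direction, independent tests:** 1 − 0.95^k.

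- k = 5: 1 − 0.95^5 = 22.6%
- k = 3 (one combined maternal score): 1 − 0.95^3 = 14.3%

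**With correlation.** The document gives no correlations, so those below are assumptions. Five correlated normal test statistics were simulated (2,000,000 draws per row).

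| Growth pair | Maternal domains | Across sets | Two-sided 5%, either direction | Two-sided 5%, favouring the app only | One-sided 5%, favouring the app |
|---|---|---|---|---|---|
| 0 | 0 | 0 | 22.6% | 11.9% | 22.6% |
| 0.80 | 0.3 | 0 | 20.3% | 10.5% | 19.5% |
| 0.90 | 0.5 | 0 | 18.7% | 9.6% | 17.8% |
| 0.95 | 0.5 | 0.2 | 18.0% | 9.0% | 16.8% |
| 0.95 | 0.7 | 0.3 | 16.2% | 8.2% | 15.0% |
| 0.70 | 0.7 | 0.7 | 14.8% | 7.4% | 13.5% |

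The benchmark for one test is 5% for either direction, 2.5% for favouring the app with a two-sided test, and 5% with a one-sided test. The independent value in the fifth column is 1 − 0.975^5 = 11.9%. With three independent outcomes it is 1 − 0.975^3 = 7.3%.

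**Both reductions together.** With growth correlation 0.90 and all else independent, the five-test simulation gives 20.3%. Removing the three maternal tests leaves (1 − 0.2033) / 0.95^3 = 0.929 as the chance that neither growth test rejects. Adding one combined maternal score gives 1 − 0.929 × 0.95 = 11.7%.

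**The case against.** **Multiplicity rules often sit in an analysis plan that is not shown.** This stands as far as it goes: the lack of an adjustment method would not be a finding alone. Which outcome is primary is a different matter. The article has an outcomes section and a heading that presupposes a ranking, yet gives none.

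**A reader might infer an 18 to 23% chance of falsely calling the app effective.** The document does not support that as a general statement. With two-sided tests, that range counts any rejection, including results against the app. Counting favourable results only, the figure is about 9 to 12% against 2.5%, and lower still with strong correlation. Figures of about 17 to 23% against 5% apply to favourable claims only if tests are one-sided. The stated sample size matches a one-sided test, but the analysis section does not say that tests will be one-sided.

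**A reader might infer that the protocol lets any one of five results establish effectiveness.** It states no such rule. That reading is an inference from the absence of a decision rule. If all five had to succeed, there would be no inflation, but that rule is not stated either.

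**The count of five may be too high.** Outcomes {12} also refers to the maternal measure as nutritional literacy, and there is a single questionnaire whose scoring is in a cited source. One combined score is possible. This stands and is why the range extends downwards.

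**The effect size may belong to a definite outcome in the cited earlier study.** That is possible. The point is only that the article does not say which.

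**Conclusion.** The concern holds as a failure to designate a primary outcome, and it should be fixed before analysis. If one significant outcome is taken as success, the rate of any false significant difference is 22.6% for five independent two-sided tests. It is about 14 to 20% under assumed correlations or one combined maternal score, and nearer 12% if both apply. All compare with 5%.

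For results favouring the app under two-sided testing, the rate is about 9 to 12% against 2.5% with five outcomes at up to moderate correlation. It is about 7 to 8% if correlations are strong or there is one maternal score.

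These figures rest on assumed correlations and on the any-one reading of success. They do not include within-group changes, which would add further routes to a claim. The inflation is more than twofold on each of these readings, so the conclusion does not depend on the exact figure.

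**What to change.** Before any unblinded analysis, by dated amendment:

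1. **Name one primary outcome** in Outcomes {12} as a between-arm comparison at 3 months, tested at two-sided 5%. Weight-for-height z is a reasonable example, because the trial enrols malnourished children and the measure does not rest on self-report by unblinded mothers. Another single outcome would also close the gap.
2. **Make the other four secondary**, tested with Holm only if the primary is significant, and otherwise reported as estimates with 95% confidence intervals. Alternatively, apply Holm across all five.
3. **State that within-group changes are descriptive** and are not evidence of effect.
4. **State in Sample size {14} which outcome d = 0.5 came from.** If it is not the named primary, restate the power for the primary at the planned size. It should not simply be declared that the existing calculation refers to the new primary.

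**Cost.** Secondary outcomes can be claimed only after the primary succeeds. Recruitment began on October 31, 2022 (Trial status), so the change needs ethics approval and a registry update as well as new text. It also brings the power into the open: at d = 0.5 and two-sided 5%, 51 per group gives 70.6%, not 80%. Holm across all five is harder still at its first step: at 0.05 / 5 = 0.01, 51 per group gives 46.3% for an outcome with d = 0.5. That favours the single primary outcome. No new data collection is needed.
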